### Sample size calculation

The chosen sample size is based partly on the available literature that examines the effects of cognitive training on healthy young and older volunteers and additional pilot data collected in our laboratory from healthy young and elderly adults. Specifically, a statistical power analysis was performed for sample size estimation, based on data from Au et al. [39], comparing the ACTIVE (right-tDCS, 20 subjects) to the CONTROL (SHAM, 22 subjects) group. The effect size (ES) in this study was 0.73, considered to be medium to large using Cohen’s criteria [55]. With an alpha = .05 and power = 0.80, the projected sample size needed with this effect size (GPower 3.1) is approximately *N* = 48 for this simplest between group comparison.

Evidence has shown that individuals with low initial performance respond better to brain stimulation [56]. As we expect ABI patients in our sample to have low baseline performance, due to our selection criteria, we may also expect them to respond better to the intervention, therefore showing larger effects. Assuming, as explained above, that larger effects could reasonably be expected in a clinical population, our proposed sample size of 40 will be adequate for the main objective of this study. A post hoc power analysis will be conducted to assess if the sample size is appropriate to detect differences in a clinical population such as ABI.

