#### Randomization and blinding

A computer programme will generate forty random flags identifying the patient’s group (20 flags equal to 1 for ACTIVE, 20 flags equal to 0 for SHAM). Flag order will then be shuffled and a participant’s unique ID (sub-01, sub-02, … sub-40) associated to a flag, following the order of attendance. The study design is double blind: participants and the assessors will not know until the end of the intervention if the participant had received active or sham brain stimulation. A member of the research team (not the assessor) will program two stimulation protocols (active and sham) on the stimulation device, which will be set to operate into blind mode. As such, the person who administers the stimulation will be blind to the details of the protocol. Meaning they will not be able to see the details of the protocol. Patients are then randomly assigned to one or the other protocol, resulting in an intervention blind both to the assessor and the patient.

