### Data collection, management, analysis, and monitoring

Accuracies and reaction times at trial level will be collected, alongside the ‘n’ level for each block. Data will continuously be monitored for completeness and consistency. Data entry will be double-checked, and data quality will be ensured based examination of ranges. Prior to statistical analysis, we will test the distribution of the scores. We will analyse the data using appropriate statistical methods, including mixed and repeated measures ANOVAs, with factors of group and test variables. Variables potentially modulating the outcome of the intervention (such as age or time since injury) will considered as regressors in the analysis. Scores that are non-normally distributed will be analysed with non-parametric tests. Significant main effects and interactions (*p* < .05) will be followed by post-hoc tests corrected for multiple comparisons. Dependent variables on the computerized tasks will include mean reaction time (RT) and accuracy (% correct). The research team will analyse the data with a combination of SPSS, JASP, R, Python, and MATLAB.

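### The planned post hoc power analysis names no effect size; on its usual meaning it only restates the p-value and cannot show whether 40 patients were enough in ABI

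*Protocol article*

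**What the plan says.** All of this is in the Sample size calculation section of the protocol article, apart from the allocation, which is under Randomization and blinding.

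- The starting point is a standardised effect of 0.73 from a study in healthy volunteers: "With an alpha = .05 and power = 0.80, the projected sample size needed with this effect size (GPower 3.1) is approximately *N* = 48". The section presents this figure as the one "for this simplest between group comparison".
- The trial nevertheless plans 40 patients, allocated as "20 flags equal to 1 for ACTIVE, 20 flags equal to 0 for SHAM". The reduction is justified by an unquantified expectation: "Assuming, as explained above, that larger effects could reasonably be expected in a clinical population", it concludes that "our proposed sample size of 40 will be adequate for the main objective of this study".
- The section then closes with the sentence at issue: "A post hoc power analysis will be conducted to assess if the sample size is appropriate to detect differences in a clinical population such as" (the sentence ends by naming ABI).

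The section gives neither the effect size nor the SD for that last analysis, and no value above which the sample would count as appropriate. The only power benchmark in the document is 0.80.

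**The concern.** The closing sentence states both a method and the question it is to answer. The question is a fair one. The cut from 48 to 40 rests on ABI patients responding more strongly than healthy volunteers, no size is given for that larger response, and this analysis is the only check on it that the article states.

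The difficulty is with the method. At fixed sample size and alpha, power computed at the observed effect carries the same information as the p-value. A small observed effect gives low observed power whether tDCS adds nothing or the trial was too small to show a real benefit, so the analysis cannot separate those two explanations. In the other direction, a strongly significant result would appear to confirm its own sample size, using an effect estimate that is large partly because it was selected for significance. Either result would be a poor basis for sizing a later ABI trial.

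**Working it through.** **Inputs.** Effect 0.73 (in SD units), alpha .05, power 0.80 and N = 40 come from Sample size calculation; 20 per arm comes from Randomization and blinding. The article does not state whether the test is one- or two-sided, so both are shown. Two assumptions are mine: the comparison is a two-sample t-test, and appropriate means power of at least 0.80.

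**1. The plan's own figure.** For a t-test with n per arm, power is the probability that a noncentral t with 2n − 2 df and noncentrality d/√(2/n) exceeds the critical value.
- One-sided, d = 0.73: 24 per arm gives power 0.801, so N = 48. This reproduces the stated figure.
- Two-sided, d = 0.73: 31 per arm is needed, so N = 62 (60 by the normal approximation).

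**2. Observed power at the significance boundary.** With 20 per arm, df = 38 and √(2/20) = 0.316.
- Two-sided: critical t = 2.024, so p = .05 corresponds to observed d = 2.024 × 0.316 = 0.640. Taking 0.640 as the true effect gives power 0.505.
- One-sided: critical t = 1.686, observed d = 0.533, power 0.504.

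Any non-significant result has a smaller observed effect and therefore lower observed power.

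**3. What it takes to pass 0.80.**
- Two-sided: observed d of at least 0.909 (t = 2.875, p ≤ .0066).
- One-sided: observed d of at least 0.801 (t = 2.532, p ≤ .0078).

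**4. How often the sample would be called inadequate (observed power below 0.80).**

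| True effect | Two-sided | One-sided |
|---|---|---|
| 0 | 1 − .0066 = 99.3% | 1 − .0078 = 99.2% |
| 0.73 | 70% | 58% |
| Effect at which real power is 80% | 49% | 49% |

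The last row shows the problem most clearly: a trial whose real power meets the target would fail this check about half the time. A simulation of 200,000 null trials for each sidedness gave 99.3% and 99.2%, and all non-significant trials fell below 0.80.

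**5. Sensitivity.** With 16 or 18 per arm the null figure stays between 99.2% and 99.3%. For a group-by-time F-test with 2 or 3 numerator df it is 99.1% or 98.7%. Observed power at p = .05 is then 0.58 or 0.64, so the 50% ceiling belongs to the two-group comparison, but both values are still below 0.80.

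**6. Power at the planning effect instead.** At d = 0.73 and 20 per arm, power is 0.61 two-sided and 0.73 one-sided. Two-sided it falls to 0.57 with 18 per arm and 0.52 with 16. Both full-sample values are below 0.80 before any patient is recruited.

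**7. The confidence interval as an alternative.** The 95% half-width is 2.024 × 0.316 = 0.64 SD. The interval excludes 0.73 when the observed d is below 0.73 − 0.64 = 0.09. With no true effect this happens in about 61% of trials, so the interval still includes 0.73 in about 39%.

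**The case against.** The strongest reply is that the sentence is underspecified rather than wrong. It names no effect size, and a further kind of post hoc power does work: take a difference fixed in advance and the SD actually seen in ABI patients. That quantity is not a function of the p-value and is not known before recruitment. With a difference of 0.73 planning SDs and 20 per arm, sampling error in the SD alone moves two-sided power between about 48% and 79% (5th to 95th percentile). It would suit the stated purpose. This stands, and it rules out any claim that no form of the analysis could answer the question. The text, however, neither specifies that form nor gives a difference to use in it.

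Two smaller replies also stand in part. Power at 0.73 is not wholly fixed in advance, because attrition and, for repeated measures, within-patient correlation affect it; even so, it would not test whether the effect in ABI is larger. And the two-sided figures are not the basis on which N = 48 reproduces, which is why both sets are given.

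A reader might infer that a null trial will be explained away as underpowered. The article does not say so. It attaches no decision to the post hoc analysis, and the inference on tDCS under Data collection, management, analysis, and monitoring relies on p < .05 without it. The post-hoc tests mentioned in that section are follow-up comparisons corrected for multiplicity and have no bearing on this point.

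**Conclusion.** The point holds in a conditional form. If the analysis uses the observed effect, it cannot answer the question set for it: observed power is about 50% at most after any non-significant two-group result. With a 0.80 pass mark, the sample is called inadequate in about 99% of trials with no effect, whichever sidedness applies, and in 70% (two-sided) or 58% (one-sided) if the true effect is 0.73. If it uses 0.73, the answer is essentially known now and does not concern ABI. Only a prespecified difference combined with the ABI SD would be informative, and that is not what is written.

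The 99% and the statement that non-significant results always fail depend on the observed-effect reading and the 0.80 cut-off. The article spells out neither, although 0.80 is its only benchmark. About 95 of those 99 points are simply non-significance under no effect, which is what restating the p-value means. The primary test, alpha and sample size are not affected, so this is a change the sponsor should make rather than a threat to the main result.

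**What to change.** Replace the post hoc power sentence with wording such as:

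> The active-minus-sham difference in the primary outcome will be reported with its 95% confidence interval. A non-significant result will be read by whether the interval excludes the reference effect of 0.73 SD used in the sample size calculation; if it does not, the result is inconclusive. Sample size for future ABI trials will use the SD observed in this trial (with its 95% CI) and a difference fixed in advance, not the observed difference.

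Here 0.73 serves as the only reference value the plan states. It is not the effect assumed for ABI, which the plan expects to be larger. With 38 df, the 95% CI for the SD runs from about 0.82 to 1.29 times the estimate, so it should be carried into any future calculation.

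The change needs no extra patients, visits or data. Its cost should be stated openly. With a half-width of 0.64 SD, about 39% of trials with no true effect would fail to exclude 0.73. About 2.5 of those points would be chance significant results in favour of tDCS (two-sided test), leaving roughly 39 − 2.5 = 36% labelled inconclusive. At a true effect of 0.3 the interval fails to exclude 0.73 in about 75% of trials. If the sponsor prefers to keep a power statement, the least it needs is a difference fixed in advance and a commitment to use the ABI SD.

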### Intervention

The BRAINSTORMING trial is designed as a randomized clinical trial, assessor and patient blinded with two parallel groups, and a simple randomization with a 1:1 allocation ratio. Participants identified as having reduced working memory will be randomly assigned to one of two experimental groups: an active (or right-sided tDCS) group and a control (or SHAM) group. Individuals included in the active group will receive 20 min of tDCS to the right dorsolateral prefrontal cortex while completing the WM training, whereas participants in the control group will complete the WM training while receiving sham (e.g., placebo) stimulation. Participant blindness to group membership will be achieved by the use of a SHAM protocol, which simulates current stimulation.

#### Randomization and blinding

A computer programme will generate forty random flags identifying the patient’s group (20 flags equal to 1 for ACTIVE, 20 flags equal to 0 for SHAM). Flag order will then be shuffled and a participant’s unique ID (sub-01, sub-02, … sub-40) associated to a flag, following the order of attendance. The study design is double blind: participants and the assessors will not know until the end of the intervention if the participant had received active or sham brain stimulation. A member of the research team (not the assessor) will program two stimulation protocols (active and sham) on the stimulation device, which will be set to operate into blind mode. As such, the person who administers the stimulation will be blind to the details of the protocol. Meaning they will not be able to see the details of the protocol. Patients are then randomly assigned to one or the other protocol, resulting in an intervention blind both to the assessor and the patient.

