**Method:**

Patients with a working memory deficit will be recruited and assigned to two age-matched groups receiving working memory training for 2 weeks: an active group, receiving tDCS (2 mA for 20 min), and a control group, receiving sham stimulation. After the end of the first 2 weeks, both groups will continue the working memory training for three more weeks. Outcome measures will be recorded at timepoints throughout the intervention, including baseline, after the 2 weeks of stimulation, at the end of the working memory training regimen and 1 month after the completion of the training.

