## Aims and objectives

The aim of this research project is to investigate the impact of combined working memory training and tDCS protocols in individuals following a brain injury in terms of the training gains, change in objective measures of working memory, mood and fatigue, as well as participants’ perceptions of day-to-day memory function and subjective benefit of the training program.

Specifically, our primary objective is to determine if the combination of tDCS and working memory training is superior to working memory training alone to improve working memory function in an n-back task in an ABI population. The key secondary objectives are to determine if the combination of brain stimulation with working memory training can:
boost performance in other cognitive domains (attention, executive functions)speed training gainslengthen improvement duration to 1 monthincrease improvement magnitude

To address the above questions, we will use a randomized clinical trial, assessor- and patient-blinded with two parallel groups and a simple randomization with a 1:1 allocation ratio.

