### Recruitment

Forty adults between the age of 18 and 69 years will be recruited through the Community Brain Injury Service. Patients will be randomly assigned to one of two experimental groups: an active (or right-sided tDCS) group and a control (or SHAM) group. All patients will receive WM training. As there is evidence that age modulates individual responses to both tDCS [50–52] and training regimens [53, 54], the two groups will be age-matched in two age subgroups: those aged between 18 and 45 years and those aged between 46 and 69 years, randomised within age range. Other factors may also influence the impact of the intervention on patients, including medications, time since injury, baseline performance, and these factors will be included as regressors in the analysis whenever appropriate. To reduce the variability due to different locations of lesions, patients with lesions underneath the electrodes (that could modify the induced electric field) will be excluded. Finally, as explained in the following, patients will only be included if they present with a working memory deficit, but no general intellectual impairment.

As the aim of this research is to improve working memory, only participants with a working memory impairment will be included. As we are focusing on improving a documented working memory deficit, we will not attempt to distinguish between pathologies (unless otherwise determined by the exclusion criteria for tDCS, e.g. a lesion underneath the electrodes), rather we will screen patients based on working memory performance. Final analysis will explore differences between pathologies. To identify a working memory impairment, cognitive tests from the Wechsler Adult Intelligence Test (WAIS-IV) and the Wechsler Memory Scale (WMS-IV) will be administered. These tests are administered to every patient as part of the routine care protocol. We will use the following scores:

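### The allocation list described ignores age, so it neither implements nor ensures the promised matching in two age bands, and *simple* is the wrong label for it

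*Protocol article*

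**What the plan says.** The article describes the allocation in four places besides its abstract.

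- **Recruitment** gives the design intention: "the two groups will be age-matched in two age subgroups", namely "those aged between 18 and 45 years and those aged between 46 and 69 years, randomised within age range". The reason offered is that "there is evidence that age modulates individual responses to both tDCS" and to training regimens. The Method paragraph of the abstract repeats it: patients are "assigned to two age-matched groups receiving working memory training for 2 weeks".
- **Aims and objectives** describes a trial "with two parallel groups and a simple randomization with a 1:1 allocation ratio".
- **Intervention** repeats the label: "and a simple randomization with a 1:1 allocation ratio".
- **Randomization and blinding** gives the procedure. A program generates forty flags, 20 for active and 20 for sham. Their order is shuffled, and each ID from sub-01 to sub-40 is "associated to a flag, following the order of attendance".

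On the analysis side, Data collection, management, analysis, and monitoring says that variables that may modulate the outcome, age among them, will be considered as regressors.

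**The concern.** The design intention and the procedure do not fit together. Randomising within age bands needs the allocation to depend on the band, through a separate list per band or an equivalent device. The procedure as written gives the next attendee the next flag whatever their age. A team that followed it to the letter would have no step at which age enters.

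The plan itself treats age as important enough to match on, and with 40 patients a chance imbalance in age band is not rare. The final report would also describe the groups as age-matched although nothing in the allocation made them so. An analysis plan cannot repair this, because allocation happens at enrolment.

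**Working it through.** **Step 1. Set the descriptions side by side.**

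| Section | Scheme described | Uses age? | Fixes 20:20? |
|---|---|---|---|
| Abstract (Method), Recruitment | Randomised within two age bands | Yes | Not stated |
| Aims and objectives, Intervention | Simple, 1:1 | No | No, by definition of simple |
| Randomization and blinding | One shuffled list of 20 + 20, by attendance | No | Yes |

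The last row is a complete algorithm: list length, arm counts, shuffle, ID range and assignment rule. It has no place for the age bands.

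**Step 2. Size of the age imbalance under the list as written.** The plan gives no figure for this, so there is none to reproduce.

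Inputs: 40 patients and 20 per arm (Randomization and blinding). The number K of patients aged 46-69 is not given. I assume K = 20 to 28.

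Let X be the number of older patients in the active arm. With one shuffled 20/20 list, X is hypergeometric:

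P(X = x) = C(K, x) · C(40 − K, 20 − x) / C(40, 20).

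The sham arm has K − X older patients, so the gap between arms is D = |2X − K|. For even K, D takes the values 0, 2, 4 and so on.

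Worked for K = 24: P(D = 0) = P(X = 12) = 0.252 and P(D = 2) = P(X = 11 or 13) = 0.414. Hence P(D ≤ 2) = 0.667 after rounding, and P(D ≥ 4) = 1 − 0.667 = 0.333.

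| K | Expected D | P(D = 0) | P(D ≤ 2) | P(D ≥ 4) | P(D ≥ 6) |
|---|---|---|---|---|---|
| 20 | 2.5 | 0.248 | 0.657 | 0.343 | 0.113 |
| 24 | 2.4 | 0.252 | 0.667 | 0.333 | 0.105 |
| 28 | 2.3 | 0.269 | 0.699 | 0.301 | 0.082 |

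The result depends little on K. Even at K = 10, P(D ≥ 4) is 0.273 and P(D ≥ 6) is 0.065.

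**Step 3. The same quantity with one blocked list per band.** I simulated block sizes of 4 and 6 chosen at random (my assumption) for the same three values of K. The expected gap in older patients falls to about 0.45. A gap of 2 occurs in about 22-23% of runs, and no run gave a gap of 4 or more. The total split is within 21:19 in about 97% of runs and 22:18 or worse in about 2.5%.

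**The case against.** Five points can be made on the other side.

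- **The harm can be overstated.** A reader might infer that age-matching cannot occur, or that age will be confounded with treatment. The documents do not support either reading. A single shuffled list is valid randomisation: it balances age in expectation, and the gap is 2 or fewer in 66-70% of cases over the assumed range. Chance imbalance is not systematic bias, and the comparison stays unbiased over randomisations. This stands, and it limits the point to a property that is promised but not ensured.
- **Age is already in view for the analysis.** That is so, but the wording commits only to considering it as a regressor. The exact model may be left to an analysis plan, so adjustment is a partial safeguard and no substitute for the promised design.
- **The label *simple* may just be loose wording.** Probably so. Literal coin-tossing would give exactly 20:20 with probability 12.5% and a split of 23:17 or worse with probability 43% (binomial, 40 trials, probability 0.5). A reader might take those as risks of this trial, but the fixed 20 + 20 list rules them out. The label is a wording error and not a competing scheme of equal weight.
- **An article condenses a fuller protocol.** This does not answer the point, because the procedure is stated in full and contradicts the intention. It does mean that what will actually be done is unknown.
- **The 20:20 total is itself not secure.** Participants' timeline places randomisation before the screening interview that can exclude patients, whereas Eligibility criteria requires the criteria to be met at randomisation. Flags could therefore be spent on excluded patients. This qualifies the exact probabilities, and stratifying does not cure it.

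**Conclusion.** The point holds in a limited form. The article promises randomisation within two age bands and then specifies a procedure that ignores age, so the matching is neither implemented nor ensured. The term *simple* also misdescribes a list with fixed totals.

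If 20 to 28 of 40 patients are in the older band and 20 are analysed per arm, there is a 30-34% chance that the arms differ by 4 or more older patients, and an 8-11% chance of 6 or more. The cost is precision and credibility on a factor the plan says modulates response. These figures count patients; I have not estimated the effect on power or on the treatment estimate, and the documents give no age effect from which to do so.

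This should be fixed before recruitment. It does not invalidate the randomised comparison.

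**What to change.** 1. In Randomization and blinding, replace the single list by two separately generated lists, one for ages 18-45 and one for ages 46-69, each in randomly varying permuted blocks. Blocks are needed because the final size of each band is not known in advance.
2. In Aims and objectives and in Intervention, replace *simple* with wording that states stratification by age band.
3. In the analysis section, commit to age band as a factor in the primary analysis.

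The cost is a few lines of code and some protocol wording. The downside is that the final split may not be exactly 20:20: it would usually be within 21:19, and 22:18 or worse about 2.5% of the time with blocks of 4 and 6.

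Dropping the matching claim and prespecifying adjustment for age would also make the text consistent, but it would give up a design property that the plan justifies on its own grounds.
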